| List of Appendices Appendix 1. Code lists for the primary outcomes |
| Amendments **Amendment 1 – 19/05/2019 (approved)**  **We clarify that aims 1 and 2 (prognostic model derivation and validation) of the study should include the whole population independently of whether patients are new or old users of preventative treatment; the causal inference analyses will focus on new users only:**  *L. Definition of the study population*  Patients will be excluded if they meet the following criteria:  Previous prescription of the exposure variable (antihypertensive, statin or antiplatelet; for causal inference analyses only)  **Amendment 2 – 28/06/2021 (approved 05/07/2021)**  **We have made the following revisions aimed at simplifying the analysis plan in light of the very large sample size and computational time required to conduct each analysis:** *C. Technical Summary / E. Objectives, Specific Aims and Rationale* Aims:  3) Use causal inference methods (multivariable regression, propensity score adjustment/matching, instrumental variable analysis) to examine whether modification of treatment could have an important impact on the risk of adverse events.  *L. Definition of the study population*  Study entry criteria – Patients will enter the cohort on the index date, defined as:   \| **Exposure** \| Antihypertensive therapy \| Statin therapy \| Antiplatelet therapy \| \| --- \| --- \| --- \| --- \| \| **Index date definition** \| 12 months after the first systolic blood pressure reading ≥130 mm Hg \| 12 months after the first coded or calculated CVD risk of ≥5% (equivalent to age ≥50 years for men and ≥60 years for women) \| 3 months after first CVD event \|   *N. Exposures, Outcomes and Covariates*  Positive controls are outcomes know to be affected by treatment (e.g. cardiovascular disease, death)  For causal inference analyses (only), sensitivity analyses will explore outcomes defined more broadly using primary care codes as well. *O. Data/ Statistical Analysis* We no longer plan to conduct an internal validation of the prediction models. The following text from the protocol is therefore redundant:  Where feasible and appropriate, each model will be internally validated using the bootstrap method, to allow optimism-adjusted estimates of calibration and discrimination performance to be obtained. Adjustment for overfitting will be undertaken using a uniform shrinkage factor identified from bootstrapping, followed by re-estimation of the cumulative baseline sub-distribution hazard function (and thus baseline cumulative incidence function) to maintain overall calibration between observed and predicted risks. Given the large sample size, overfitting is likely to be small (see sample size calculation above). If bootstrapping is computationally infeasible due to the large sample size, then a smaller random sample of the population will be used or alternative internal validation methods employed such as cross validation.  *Aim 3 – causal inference analysis*  For most of the outcomes described in this proposal, the association and magnitude of effect with treatment is not well defined in randomised controlled trials. We will therefore undertake causal inference work to examine whether modification of treatment could have an important impact on the risk of adverse events using two causal inference methods: multivariable adjustment, propensity score adjustment/matching and instrumental variable analysis.  For the analysis using multivariable adjustment, Cox proportional hazards models will be used to compare adverse event rates in each experimental group. Estimates will be adjusted for pre-specified variables thought to confound the relationship between treatment and adverse events.  For the analysis using propensity scores, we will conduct separate analyses adjusting for propensity score and matching via propensity score.  *Subgroup and sensitivity analyses*  Where possible and appropriate, analyses of treatment associations will be examined in subgroups of the population. These will include age, sex, baseline blood pressure and cardiovascular risk, by drug type/dose/intensity and past medical history. Subgroup definitions will be agreed by expert opinion or taken from an accompanying systematic review of previous trials, examining the same topic. For computational reasons (whereby only one imputation model is required for all subgroup analyses of each outcome), these analyses will only be undertaken using propensity score adjustment. *P. Plan for addressing confounding* Two approaches will be taken to determine whether observed associations are potentially subject to residual confounding.^46^ Where all approaches provide similar results, we can be more confident that the findings are accurate and reliable. Further steps will be taken to examine the validity of treatment effect estimates using positive and negative controls: the impact of treatment on an outcome known to be affected by treatment (e.g. cardiovascular disease and death; positive controls)  **Amendment 3 – 25.11.2021**  **We have added exploratory analyses using supervised machine learning approaches to address missing data and deal with confounding by indication in the causal inference analyses.** O. Data/ Statistical Analysis ***Aim 3 – causal inference analysis***  For most of the outcomes described in this proposal, the association and magnitude of effect with treatment is not well defined in randomised controlled trials. We will therefore undertake causal inference work to examine whether modification of treatment could have an important impact on the risk of adverse events using two causal inference methods: propensity score matching and instrumental variable analysis.  For the propensity score analysis, eligible patients will be matched 1:1 at the index date using propensity scores, which indicate the likelihood a patient will be prescribed treatment on the basis of their known (pre-treatment) characteristics and other known information which might influence the decision to treat. Predictors of preventative drug prescription will be explored in a logistic regression model. Matched patients will be compared using the Cox proportional hazards models, but hazard ratios will only be adjusted by factors unbalanced at baseline which are not already included in the propensity score model. Time since cohort entry will be used as the underlying time function in each model.  For the instrumental variable analysis, GP’s previous antihypertensive prescribing preferences will be used as an instrument to predict the likelihood of actual treatment. Risk of adverse events will be estimated in patients attending a GP considered a high prescriber of preventative medication and compared to those attending a GP considered a low prescriber. If the results from the propensity score matching suffer from unmeasured confounding, they will differ from those of the instrumental analysis. If this is the case, these models will be refined with additional factors to achieve better adjustment and matching. Where all approaches provide similar results, we can be more confident that the findings are accurate and reliable.^46^  Generative Adversarial Networks (GAN) will also be used to impute missing counterfactual data (unobserved effects of untaken treatments) on an individual level. GAN models are a class of machine learning frameworks that involves the simultaneous training of a pair of deep neural networks in competition with each other. The idea is that the first network, the generator, generates synthetic data samples that are similar to the original samples, while the second network, the discriminator, evaluates the authenticity of the generated samples [1]. Data similarity and fidelity are usually evaluated using well-known metrics such as Maximum Mean Discrepancies [2] and Jensen-Shannon Divergence [3]. While GAN’s initial uses were for imaging applications, its generative capabilities make it naturally suitable for generating missing values that can be used to impute the original samples.  In this work, we build on the intuition that treatment effects estimation and causal inference are a missing data problem, where counterfactuals (unobserved effects of untaken treatments) are missing [4]. Specifically, we plan to use GAN to impute missing counterfactual data, for the samples available in CPRD. By modifying the generator’s goal to accurately impute missing data, and the discriminator’s goal to distinguish between observed and imputed counterfactual values for the same patient record. The model can generate the missing data conditional on the observed values and assigned treatment for each patient as seen in [5, 6]. While useful, the work of [5, 6] are not compatible for time-series data nor for estimating multiple treatment effects, which limits its use in real-life treatment applications. Therefore, we plan to extend such previous works to make them compatible for multiple treatment options and for time-series data to allow for long-term treatment (antihypertensives, statins, antiplatelets) estimation effects for multi-morbid populations as initially proposed in this project.  The proposed GAN approach does not generate new patient samples, but rather generates counterfactual (missing component) conditioned on observed factual data, and outputs a complete record with both factual and counterfactual outcomes to allow for treatment effect estimation for each patient. This approach is naturally immune to re-identification attacks since no new samples are generated, but we will run privacy checks and measures within the data to verify that the model is not copying potential outcomes from patients in the training sample. Example privacy measures that we plan to apply include empirical evaluations such as mathematical privacy definitions such as identifiability [7] that quantifies the probability of re-identification to ensure that no combination of attributes could reveal the identity of a patient. Other privacy evaluation methods include testing that the model is robust against membership inference attacks, where an attacker attempts to determine if a specific patient was used in the training set of the model [8]. Lastly, we will experiment with strict theoretical guarantees such as differential privacy which allow for the model to learn almost nothing about an individual while learning useful information about a population [9].  **References**  [1] Ian Goodfellow, Jean Pouget-Abadie, Mehdi Mirza, Bing Xu, David Warde-Farley, Sherjil Ozair, Aaron Courville, and Yoshua Bengio. Generative adversarial nets. *Advances in neural information processing systems*, 27:2672–2680, 2014.  [2] Arthur Gretton, Karsten M Borgwardt, Malte J Rasch, Bernhard Sch¨olkopf, and Alexander Smola. A kernel two-sample test. *The Journal of Machine Learning Research*, 13(1):723–773, 2012.  [3] AP Majtey, PW Lamberti, and DP Prato. Jensen-shannon divergence as a measure of distinguishability between mixed quantum states. *Physical Review A*, 72(5):052310, 2005.  [4] Peng Ding and Fan Li. Causal inference: A missing data perspective. *Statistical Science*, 33(2):214– 237, 2018.  [5] Jinsung Yoon, James Jordon, and Mihaela Schaar. Gain: Missing data imputation using generative adversarial nets. In *International Conference on Machine Learning*, pages 5689–5698. PMLR, 2018.  [6] Jinsung Yoon, James Jordon, and Mihaela van der Schaar. Ganite: Estimation of individualized treatment effects using generative adversarial nets. In *International Conference on Learning Representations*, 2018.  [7] Jinsung Yoon, Lydia N Drumright, and Mihaela Van Der Schaar. Anonymization through data synthesis using generative adversarial networks (ads-gan). *IEEE journal of biomedical and health informatics*, 24(8):2378–2388, 2020.  [8] Reza Shokri, Marco Stronati, Congzheng Song, and Vitaly Shmatikov. Membership inference attacks against machine learning models. In *2017 IEEE Symposium on Security and Privacy (SP)*, pages 3–18. IEEE, 2017.  [9] Cynthia Dwork, Aaron Roth, et al. The algorithmic foundations of differential privacy. *Found. Trends Theor. Comput. Sci.*, 9(3-4):211–407, 2014.  **Amendment 4 – 30.11.2022**  **Added University of Birmingham to the list of data processors.** |

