**PART 2: PROTOCOL INFORMATION**

| **Applicants must complete all sections listed below**  **Sections which do not apply should be completed as ‘*Not Applicable’* and justification provided** |
| --- |
| Study Title (Max. 255 characters) Understanding the harms of antihypertensives, statins and antiplatelets for prevention of cardiovascular disease: A prognostic modelling and casual inference study |
| Lay Summary (Max. 250 words) People are living for longer, with more long-term physical and mental conditions which worsen their health. One example is high blood pressure, where people can take 3-4 drugs to prevent stroke. However, dozens of people have to be treated for at least a year to prevent a stroke in one person. This is because these drugs only reduce the possibility of stroke, they do not remove it altogether. Some of these patients may be prone to side effects such as falls and kidney problems which may be more common than any benefits.  This proposal aims to use information from the medical records from hundreds of thousands of patients to establish the link between drugs used to prevent heart attack and stroke and side effects. We will focus on drugs that lower blood pressure (known as antihypertensives), lower cholesterol (known as statins) or prevent blood clots (known as antiplatelets). This information will be used to develop a calculator which predicts a person’s risk of experiencing side effects. This calculator will form part of a support tool which will help patients and doctors make better informed decisions about starting or continuing drugs. |

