| Definition of the Study population Individual patient data will be extracted from the medical records of all patients registered at linked general practices contributing to the CPRD GOLD and Aurum in England.  Patients will be included if they meet the following criteria:   - Patients over the age of 40 years - Registered to a CPRD ‘up-to-standard’ practice - Records available after the study start date (01/01/1998) - Sufficient data to define the index date (see table below)   Patients will be excluded if they meet the following criteria:   - Previous prescription of the exposure variable (antihypertensive, statin or antiplatelet) - Blood pressure >180 mm Hg or total cholesterol >7.5 mmol/L (in patients with high blood pressure or cholesterol, treatment is indicated regardless of risk)   Study entry criteria – Patients will enter the cohort on the index date, defined as:   \| **Exposure** \| Antihypertensive therapy \| Statin therapy \| Antiplatelet therapy \| \| --- \| --- \| --- \| --- \| \| **Index date definition** \| 12 months after the first systolic blood pressure reading ≥130 mm Hg \| 12 months after the first coded or calculated CVD risk of ≥5% \| 3 months after first CVD event \|   Study exit criteria   - Last date at which the most recent linked data are available from the CPRD (study end date, July 2018) - Date of the most recent data upload from the practice to which a given patient is registered - Date at which a given patient transfers out of a registered CPRD practice - Date of death or specific outcome of interest |
| Selection of comparison group(s) or controls Aim 1: Not applicable – single cohort in CPRD GOLD.  Aim 2: Not applicable – single cohort in CPRD AURUM.  Aim 3 will use propensity score matching and instrumental variable analysis – see Methods section below. |

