| Data/ Statistical Analysis **Prognostic modelling**  ***Aim 1 – prognostic model derivation (primary analysis)***  Where feasible and appropriate, flexible parametric survival models will be derived in the CPRD GOLD for each outcome separately. Baseline survival over time will be estimated using the Royston-Parmar approach of restricted cubic splines on the cumulative log hazard scale. In contrast to Cox regression, this allows a smoothed estimate of the baseline survival function to be derived, and the time period of prediction to be varied, facilitating individualised risk prediction. For the primary analysis, a 10-year period of prediction will be considered. Further sensitivity analyses will be conducted examining a 5-year period. Where insufficient data are available, or modelling procedures become prohibitively complex (computationally), simpler approaches such as Cox regression will be considered.  Each drug class (prescribed in the 12 months prior to the index date) will be entered into the model as a binary variable to allow for multiple treatments to be considered in each model. Where appropriate, models will be constructed with all other variables entered as continuous (not categorised) variables, and potential non-linear trends will be examined. Transformations or fractional polynomials will be used if non-linear trends are detected. Where hazard ratios are not proportional, interactions of effects with time will be included. Further interaction terms, identified in an accompanying systematic review, accounting for treatment effects which differ across specific populations may be included. Where appropriate, models will be reduced and candidate predictors selected for inclusion based on p values of association. Time since cohort entry will be used as the underlying time function in each survival model.  In a further analysis, we will extend the modelling process as described above to account for competing risk of death from other causes. This will produce a model that predicts the risk of adverse events from cardiovascular treatment over time, in the real world where individuals might die from other causes and thus prevent cardiovascular treatment adverse events from occurring. We will again use a flexible parametric modelling framework to estimate the sub-distribution hazard and cause-specific cumulative incidence functions.^45^  Missing data will be handled, under a missing at random assumption, using multiple imputation (see below) followed by Rubin’s rules to combine parameter estimates across studies.  Where feasible and appropriate, each model will be internally validated using the bootstrap method, to allow optimism-adjusted estimates of calibration and discrimination performance to be obtained. Adjustment for overfitting will be undertaken using a uniform shrinkage factor identified from bootstrapping, followed by re-estimation of the cumulative baseline sub-distribution hazard function (and thus baseline cumulative incidence function) to maintain overall calibration between observed and predicted risks. Given the large sample size, overfitting is likely to be small (see sample size calculation above). If bootstrapping is computationally infeasible due to the large sample size, then a smaller random sample of the population will be used or alternative internal validation methods employed such as cross validation.  ***Aim 2 – prognostic model validation***  External model validation will be undertaken using data from CPRD Aurum. The accuracy of risk predictions from each model will be assessed with calibration plots and 5 and 10 years, calibration measures (slope, E/O statistics), measures of overall fit (using pseudo-R^2^ estimates) and discrimination measures (C-statistics and D-statistics).  ***Aim 3 – causal inference analysis***  For most of the outcomes described in this proposal, the association and magnitude of effect with treatment is not well defined in randomised controlled trials. We will therefore undertake causal inference work to examine whether modification of treatment could have an important impact on the risk of adverse events using two causal inference methods: propensity score matching and instrumental variable analysis.  For the propensity score analysis, eligible patients will be matched 1:1 at the index date using propensity scores, which indicate the likelihood a patient will be prescribed treatment on the basis of their known (pre-treatment) characteristics and other known information which might influence the decision to treat. Predictors of preventative drug prescription will be explored in a logistic regression model. Matched patients will be compared using the Cox proportional hazards models, but hazard ratios will only be adjusted by factors unbalanced at baseline which are not already included in the propensity score model. Time since cohort entry will be used as the underlying time function in each model.  For the instrumental variable analysis, GP’s previous antihypertensive prescribing preferences will be used as an instrument to predict the likelihood of actual treatment. Risk of adverse events will be estimated in patients attending a GP considered a high prescriber of preventative medication and compared to those attending a GP considered a low prescriber. If the results from the propensity score matching suffer from unmeasured confounding, they will differ from those of the instrumental analysis. If this is the case, these models will be refined with additional factors to achieve better adjustment and matching. Where all approaches provide similar results, we can be more confident that the findings are accurate and reliable.^46^  A similar approach will be applied to secondary outcomes, for example, memory loss which has been hypothesised as being linked with statins^47^ and is a concern of many patients in practice, but there is no evidence to support this association from trials.^48^ We recognise that the evidence base may change for some outcomes over the next few years, and so the need to test the associations between treatment and certain outcomes may change.  *Subgroup and sensitivity analyses*  Where possible and appropriate, analyses of treatment associations will be examined in subgroups of the population. These will include age, sex, baseline blood pressure and cardiovascular risk, by drug type/dose/intensity and past medical history. Subgroup definitions will be agreed by expert opinion or taken from an accompanying systematic review of previous trials, examining the same topic.  Sensitivity analyses will be undertaken examining risk models for outcomes defined according to both hospital and primary care records. We will also explore the impact of our definition of myopathy and muscle pain, focussing on formal diagnostic codes for myopathy only. Models utilising a 5-year follow-up will be examined as a further sensitivity analysis. The primary analyses will examine the association between treatment and outcomes, assuming treatments are not altered or modified in the future. Where possible, sensitivity analyses will examine treatment entered as time varying covariates, and censor patients who have treatments removed or switched following the index date. |

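### After Amendment 1, one yes/no drug term covers both recent starters and established users, so the Aim 1 and 2 models give both the same risk

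*Protocol*

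**What the plan says.** Amendment 1 (Protocol, Amendments) lifts the previous-prescription exclusion for model derivation and validation: these aims "should include the whole population independently of whether patients are new or old users of preventative treatment". The exclusion stays for Aim 3, where "the causal inference analyses will focus on new users only".

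The Aim 1 text under Data/Statistical Analysis fixes the coding: "Each drug class (prescribed in the 12 months prior to the index date) will be entered into the model as a binary variable". It also fixes the clock: "Time since cohort entry will be used as the underlying time function in each survival model". Amendments 2 to 4 change neither.

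Definition of the Study population sets the index date. For antihypertensives it is "12 months after the first systolic blood pressure reading ≥130 mm Hg"; for statins it is the same interval after a first qualifying risk score; for antiplatelets it is "3 months after first CVD event".

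The Lay Summary says that the support tool is to help patients and doctors "make better informed decisions about starting or continuing drugs".

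**The concern.** Established users at index are people who have stayed on the drug. Patients who had an early side effect and stopped are not among them. Recent starters have not been through that selection. After Amendment 1 both groups sit under the same indicator, with no term for duration or for new versus established use, so the model cannot tell them apart.

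Where harm is concentrated early in treatment, the pooled coefficient lies between the two true values: too low for recent starters, too high for established users. For harms that build up with duration the direction could reverse. In both cases the model averages over two groups that face different questions.

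The validation step as written would not find this. If Aurum has a similar mix of users, the two errors offset and overall calibration can look good. Amendment 2 removes internal validation, so Aurum is the only performance check left.

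**Working it through.** The protocol gives no count or share of new and established users and no early hazard ratio, so there is no stated figure to reproduce. The check has two parts.

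**1. Does any stated provision separate the two groups?**

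- Time interactions (Aim 1, where hazards are not proportional) run from cohort entry. That origin is the same for both groups, so the interaction gives both the same curve.
- Interactions for specific populations are optional and drawn from a systematic review. Duration of use is not mentioned.
- The sensitivity analyses with time-varying treatment, and with censoring at removal or switch, concern changes after index, not use before it.
- Previous adverse events are a listed covariate. This partly captures people with a recorded early harm, but it does not mark who is a recent starter.
- Aim 2 lists calibration plots, slope and E/O at 5 and 10 years, with no split by user status.

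None of these separates starters from established users.

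**2. How large could the error be?**

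Assumptions, none from the protocol: starters have HR 1.5 in years 1 to 2 of follow-up and 1.0 afterwards; established users have HR 1.0 throughout; s is the starter share among users. Baseline hazard is constant and events are rare enough for hazard ratios to approximate risk ratios.

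Starters' average HR:

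- over 10 years: (2 × 1.5 + 8 × 1.0)/10 = 1.10
- over 5 years: (2 × 1.5 + 3 × 1.0)/5 = 1.20

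Pooled HR = exp(s × ln HR of starters). Shortfall for starters = 1 − pooled HR / starters' HR. Excess for established users = pooled HR − 1. The early rows allow the planned time interaction, so the pooled early HR is 1.5 to the power s.

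| | s = 20% | s = 50% | s = 80% |
|---|---|---|---|
| 10 years: pooled HR (starters 1.10) | 1.019 | 1.049 | 1.079 |
| starters too low by | 7% | 5% | 2% |
| established users too high by | 2% | 5% | 8% |
| 5 years: pooled HR (starters 1.20) | 1.037 | 1.095 | 1.157 |
| starters too low by | 14% | 9% | 4% |
| Years 1–2: pooled HR (starters 1.5) | 1.084 | 1.225 | 1.383 |
| starters too low by | 28% | 18% | 8% |
| established users too high by | 8% | 22% | 38% |

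Cross-check with a simple weighted mean of rate ratios, s × 1.5 + (1 − s) × 1.0, for the early period: 1.10, 1.25 and 1.40. These give shortfalls of 27%, 17% and 7%, so the pooling rule matters little.

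If established users also carry an excess, the gap narrows: with 1.5 and 1.2 at an even split the weighted mean is 1.35, and 1.35/1.5 = 0.90, a shortfall of 10%.

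**The case against.** Four arguments on the other side have weight.

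- *Established users may not dominate.* A reader might infer that a starter's risk is drawn mostly from people who already tolerate the drug. The protocol does not support that. It gives no share, and the index dates work against it: for antihypertensives and statins the look-back is the year after the qualifying reading or score, and for antiplatelets it includes the three months after the event. People who began because of the reading, score or event fall inside it.
- *A person about to start is not coded as a user.* At prediction that person has the drug term set to no. The Objectives separate baseline risk from the modifying effect of treatment, and Aim 3 examines the latter in new users. A reader might infer that the calculator will read a would-be starter's risk off the drug coefficient; the protocol nowhere says so. Nor does it rule this out or say how the two parts combine.
- *Early error is easily overstated.* Applying the ten-year pooled HR of 1.019 to the first two years would give a 32% shortfall (1.019/1.5 = 0.68). That ignores the planned time interactions, and two years is not a planned horizon; the plan names 10 and 5 years.
- *Including current users is legitimate.* This stands in full. It suits decisions about continuing. The fault is the undifferentiated term.

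Calibration by user type could be left to an analysis plan. The single yes/no coding could not, because the protocol itself fixes it.

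**Conclusion.** The point holds in a limited form. The Aim 1 and 2 models cannot distinguish recent starters from established users, and no stated step would reveal the resulting miscalibration. If early harm is higher in starters, their predicted risk is too low and that of established users too high.

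The size cannot be fixed from the protocol. Under the assumed hazard ratios, starters' risk is about 7%, 5% or 2% too low over ten years at starter shares of 20%, 50% or 80%, and about 28%, 18% or 8% too low in the early period. The overstatement for established users over ten years is slight (2% to 8%). These figures illustrate the mechanism; they are not estimates.

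This is a worthwhile and inexpensive improvement to a model intended for a public calculator. It does not show that the calculator will mislead people who have not yet started.

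**What to change.** In Aims 1 and 2:

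1. Keep the class indicators. For each drug group add one established-user term, for people prescribed in the look-back whose first prescription in that group was more than 12 months before index, with its interaction with time. Say where former users are placed; under the present coding those who stopped more than 12 months before index count as non-users.
2. In Aurum, report calibration at 5 and 10 years separately for non-users, recent starters and established users.
3. State that the Aim 1 drug term is not the risk of a person who has not yet started, and that the effect of starting comes from the new-user analysis in Aim 3. The new term does not remove the need for this: recent starters may have begun up to 12 months before index, so some of their early harm falls before time zero.

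Cost: one or two extra parameters per model, to be counted against the maximum of 40 in the sample size section, and slightly less precise drug terms for rare outcomes. No new data are needed, since Aim 3 already requires the prescription history that identifies new users.
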